**Results:**

Ethics approval was obtained in January 2019, and recruitment of participants began in June 2019. Recruitment has been conducted via social media, web-based communities, and physician referrals. To date, 52 participants have been recruited to the e-CBT group, and 48 patients have been recruited to the in-person CBT group. Data collection is expected to be completed by March 2021, and analyses are expected to be completed by June 2021, as linear regression (for continuous outcomes) and binomial regression analysis (for categorical outcomes) are still being conducted.

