## Methods

### Study Design

For this study, an open-label, nonrandomized controlled trial study design will be used to compare the efficacy and feasibility of the web-based program with the in-person treatment option in a controlled manner. Blinding will not be possible, as patients will be aware of whether their treatment is occurring in person or remotely. Qualitative focus groups will be conducted with patients to gather personal, social, and cultural factors. These focus groups will be conducted to allow for a natural and open conversation on how participant factors can impact the treatment experience with the program. Additional focus groups will be conducted with therapists to gather information regarding the feasibility of implementing a web-based psychotherapy tool. This will be done to better understand how web-based treatment compares with in-person in terms of usability, time efficiency, and perceived connectedness to patients. These focus groups will occur posttreatment.

Quantitative analyses of e-CBT treatment efficacy will be conducted using standardized and clinically validated symptomology questionnaires. This data collection will occur at baseline, at week 6 and week 12 (posttreatment), and at a 6-month follow-up. In addition, a qualitative analysis of focus group interviews will be conducted with theme extraction. We hypothesize that the e-CBT program will offer results comparable with those of the in-person treatment program regarding symptom reduction and quality of life improvement. On the basis of this design, both the efficacy and feasibility of the e-CBT program can be evaluated and compared with in-person treatment for MDD. All study procedures have been approved by the Queen’s University Health Sciences and Affiliated Teaching Hospitals Research Ethics Board (HSREB; file number 6020045).

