### Participants

Patients (N=110; 55 e-CBT participants and 55 in-person CBT participants) aged between 18 and 65 years will be recruited from Queen’s University from the outpatient psychiatry clinic at both the Kingston Health Sciences Center sites (Hotel Dieu Hospital and Kingston General Hospital) as well as from Providence Care Hospital located in Kingston, Ontario, Canada. Additionally, family doctors, physicians, clinicians, and self-referrals will be accepted. Once informed consent is provided, a psychiatrist from the research team will evaluate participants through a secure video appointment to make or confirm a diagnosis of MDD using the Diagnostic and Statistical Manual of Mental Disorders, 5th edition [31].

The inclusion criteria for the study are as follows: aged at least 18 years at the start of the study, diagnosed with MDD according to Diagnostic and Statistical Manual of Mental Disorders, 5th edition by an attending psychiatrist from the research team, competence to consent to participate, ability to speak and read English, and consistent and reliable access to the internet. Exclusion criteria are as follows: active psychosis, acute mania, severe alcohol or substance use disorder, and/or active suicidal or homicidal ideation. If a participant is receiving another form of psychotherapy, they will also be excluded from the study to avoid any confounding effect on the efficacy of this e-CBT program. Participants are eligible for the study if they are receiving pharmacotherapy. However, they must be receiving the same drug and dosage for the duration of the study. If eligible for the study, participants will choose between the e-CBT program (n=55) or the in-person CBT offered individually through this program at Hotel Dieu Hospital (n=55).

During the informed consent process, all participants will be explained that this program is not a crisis resource and that they will not always have access to their therapist. In the case of an emergency, participants will be directed to the proper resources (eg, emergency department or crisis lines), and this event will be reported to the principal investigator of the study. The reasoning behind having a nonrandomized design and allowing patients to choose their treatment is to mimic a real-world setting in which patients have autonomy in their treatment decisions. We recognize that this could be a limitation of this study. We plan to conduct a randomized controlled trial in the future.

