### Data Analysis

This is a confirmatory study with previously established objectives and analyses. Initially, all data are examined for missing, nonsensical, and outlying variables. Missing data are treated as missing and not imputed (ie, will be analyzed on a per-protocol basis). The participants in this study were intentionally oversampled to account for dropouts or withdrawals. On the basis of previous research, an anticipated dropout rate of up to 30% was factored in. Using the PHQ-9 as the primary outcome, a 30% change is considered clinically significant. Therefore, a sample size of 55 participants in each arm of the study would be sufficient for detecting significant results with *P*=.05 and a power of 0.95. Data collection occurs at baseline (preintervention), in the middle of the study (week 6), immediately after the intervention (week 12), and at a 6-month follow-up. Using Mann-Whitney *U* tests, demographic information can be compared between participants who complete the program and those who withdraw prematurely in the hope of identifying possible differences between the two. Moreover, an intention-to-treat analysis will be conducted to evaluate the clinical effects of treatment on participants who withdraw prematurely. Linear regression analysis (for continuous outcomes) and binomial regression analysis (for categorical outcomes) will be used to identify variables associated with the outcome measures (PHQ-9, Quick Inventory of Depressive Symptomatology Questionnaire, and Quality of Life and Enjoyment Questionnaire). This will occur over the 4 measurement time points while controlling for demographic variables, including age and gender. In addition, a comparative analysis between both groups’ questionnaire scores will be conducted at all data collection time points using group and paired two-tailed *t* tests.

Other quantitative measures for the e-CBT group will be gathered by extrapolating recorded information directly through the OPTT platform (eg, the number of log-ins per day and the amount of time spent logged in). Qualitative measurement analyses will be conducted to inquire about the role of personal, social, and cultural factors in enabling or constraining the use of e-CBT. The findings will identify factors related to the utility, feasibility, and accessibility of e-CBT from the perspectives of users and providers. Interpretive qualitative methods are ideal for gathering in-depth descriptions of user experience and meaning.

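### Patients choose their arm, but the only between-arm comparison specified is an unadjusted t test, so it is open to confounding by baseline severity and other factors tied to that choice

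*Protocol article*

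**What the plan says.** The Study Design section states that "an open-label, nonrandomized controlled trial study design will be used". The Participants section says how patients reach an arm: "participants will choose between the e-CBT program (n=55) or the in-person CBT offered individually". It justifies this as reflecting real-world care, adds "We recognize that this could be a limitation of this study", and leaves randomization to a future trial.

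The Data Analysis section opens with "This is a confirmatory study with previously established objectives and analyses". Three parts of it bear on the arms:

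- **Between-arm comparison.** A comparison of both groups' "questionnaire scores will be conducted at all data collection time points using group and paired two-tailed" t tests. No covariate is mentioned.
- **Regression.** Linear and binomial models are meant to find variables associated with the outcomes over the four time points, "while controlling for demographic variables, including age and gender". Study arm is not named as a term, and neither is the baseline score.
- **Mann-Whitney tests.** These compare the demographics of completers and of those who withdraw, not of the two arms.

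The Outcome Evaluation section words the primary outcomes as changes in depressive symptoms and has the questionnaires collected at baseline. Pharmacotherapy is permitted if drug and dosage stay the same. On entry routes the abstract says: "Recruitment has been conducted via social media, web-based communities, and physician referrals".

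**The concern.** When patients pick their treatment, the arms need not be alike at the start. The article's own Background gives reasons why people might prefer web delivery: living far from services, seeking care outside working hours, fear of stigma, and isolation during the pandemic. Recruitment began in June 2019 and data collection was to run to March 2021. The in-person arm required weekly hospital visits, so the mix of patients choosing each arm may also have shifted over time. Any of these could go with severity or prognosis.

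An unadjusted t test attributes all of the follow-up difference to treatment. The hypothesis is that the two treatments give comparable results, so confounding can do harm in two ways: it can produce a difference where there is none, or hide a real one behind an apparent similarity. This is the trial's central comparison.

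**Working it through.** **Which analysis carries the arm comparison.** Paired t tests address change within an arm. The regressions look for predictors of outcome and do not name arm. That leaves the group t test, which has no covariates. It could be applied to follow-up scores (the Data Analysis wording) or to change scores (the Outcome Evaluation wording), so both are worked through.

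**Inputs from the article.** 55 per arm and anticipated dropout of up to 30%, which leaves 55 × 0.70 = 38.5, taken as 38 per arm. Two-tailed tests, with P=.05 as the significance level.

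**Inputs assumed, because the article gives none.** PHQ-9 SD within arm 5.5, the same at baseline and week 12. Correlation r between baseline and week 12 of 0.5 (range 0.4 to 0.6). Baseline gap G of 2 points, with 3 as a second case. The true treatment effect is zero and, given the baseline score, the arms would otherwise have the same expected week 12 score.

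**Bias.**

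- Follow-up scores: r × G = 0.5 × 2 = 1.0 point (0.8 to 1.2 over the range of r).
- Change scores: (r − 1) × G = (0.5 − 1) × 2 = −1.0 point (−1.2 to −0.8). The sign is reversed, but the bias is not removed.

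**Type I error of the follow-up test.** SE = 5.5 × √(2/n), and the rejection probability is P(|Z + bias/SE| > 1.96).

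| n per arm | SE | G | Bias | Bias/SE | Type I error |
|---|---|---|---|---|---|
| 38 | 1.262 | 2 | 1.0 | 0.793 | 12.4% |
| 55 | 1.049 | 2 | 1.0 | 0.953 | 15.9% |
| 38 | 1.262 | 3 | 1.5 | 1.189 | 22.1% |
| 55 | 1.049 | 3 | 1.5 | 1.430 | 29.8% |

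**Type I error of the change-score test.** The SD of change is 5.5 × √(2(1 − r)). At r = 0.5 this equals 5.5, so the error rates are the same as in the table.

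**Sensitivity to r, for G = 2.**

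| n per arm | Test | r = 0.4 | r = 0.6 |
|---|---|---|---|
| 38 | Follow-up | 9.7% | 15.8% |
| 55 | Follow-up | 11.9% | 20.8% |
| 38 | Change | 14.0% | 10.9% |
| 55 | Change | 18.1% | 13.7% |

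**Effect of adjusting for baseline.** Under the same model, a regression on arm and baseline score has no bias from this source. Its residual variance is multiplied by 1 − r² = 0.75 (0.84 to 0.64), a reduction of 25% (16% to 36%). The larger type I errors at 55 per arm show that more patients do not help: the bias stays fixed while the standard error shrinks.

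**The case against.** The strongest reply is that this is a condensed article. The word *including* makes age and gender examples, a full covariate list normally belongs in an analysis plan, and nothing excludes arm, baseline score or medication from the regression. That stands to this extent: a reader might infer that the investigators decided not to adjust for baseline severity, and the article does not show that. It does not mention such adjustment. But the article does not leave the method open either. It names the between-arm test and the class of control variables, in a study it calls confirmatory, and baseline severity is not a demographic variable.

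A reader might also infer that the plan does nothing about non-randomization. That goes too far. The limitation is disclosed, the regressions control for demographics, and group tests at every time point include baseline, so a severity gap would at least be visible. Seeing a gap does not remove it from the week 12 comparison, however.

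A third reply is that the primary outcome is change, which already uses the baseline. Change scores correct for baseline differences only in special circumstances; under the model above they over-correct by (1 − r) × G.

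Finally, the gap, the SD and the correlation are all assumed, and it is conjecture that medication, referral route or enrolment date drove the choice of arm. This is correct. It limits the claim to exposure to bias, not demonstrated bias.

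**Conclusion.** The point holds as a mismatch between design and stated analysis: arms are self-selected, the specified arm comparison is unadjusted, and the regression as described is not clearly an arm comparison at all. The comparison is open to confounding by baseline severity and other factors related to choice, whether follow-up or change scores are tested.

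Neither the size nor the direction of any bias can be determined from the article. The formulas r × G and (r − 1) × G assume equal SDs at the two times and that the baseline score captures the relevant difference between arms. The rates of about 12% to 16% for a 2-point gap are illustrative and rest on an SD of 5.5 and r = 0.5. The article does not support the stronger statement that the comparison *is* biased. Nor would adjustment make it equivalent to a randomized comparison, since unmeasured reasons for choosing an arm would remain.

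**What to change.** - Make the primary arm comparison a regression with terms for arm, baseline score of the same questionnaire, age and gender. Add pharmacotherapy status, referral route and enrolment date where these were recorded; the article does not show that they are held as analysis data.
- Report standardized baseline differences between the arms.
- Keep the unadjusted t tests as descriptive.
- Word the conclusion as an adjusted association and say that unmeasured confounding remains.
- State when the change was made. The abstract describes regression analyses as still in progress, so the adjusted model should be labelled as introduced at that stage if that is the case.
- Propensity-score weighting on the same variables is an optional sensitivity analysis.

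The cost is revised analysis text, some programming and a few degrees of freedom. Baseline scores are already in the data collection schedule, so no new patients or visits are needed.

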**Objective:**

This study aims to investigate the efficacy and feasibility of implementing an e-CBT program compared with in-person treatment for MDD. It is hypothesized that the e-CBT program will offer results comparable with those of the in-person treatment program, regarding symptom reduction and quality of life improvement.

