## Discussion

### Comparison With Prior Work

MDD is a debilitating mental illness. Although treatment options are available, these modalities are either not efficacious for patients, inaccessible, or not scalable to a large population. Therefore, an innovative treatment that is efficacious and accessible while having an increased care capacity is needed. Developing a web-based psychotherapy tool with predesigned therapy modules and care processes can drastically increase care capacity for an overwhelmed mental health care system without sacrificing the quality of care. In this study, we aim to evaluate the feasibility and efficacy of this method of care delivery. By evaluating both the efficacy (through validated symptomology questionnaires) and feasibility (using focus groups), we can learn more about the real-world usefulness of e-CBT. Many of the current options for e-CBT are offered in nonsecure, nonscalable formats (email) or less effective (self-help) modalities, and by using this web-based platform, we can fill the gaps in the literature surrounding a large-scale psychotherapy clinic format for e-CBT delivery. Through the focus group findings, we can continue to better understand the accessibility issues associated with the remote delivery of mental health treatments and use these findings to develop more accessible options for patients. If proven feasible and efficacious, a web-based psychotherapy clinic can provide significant financial savings to the health care system through efficient use of clinician time, while providing an equitable and accessible method of treatment delivery for patients.

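### Paired t tests are listed within the between-group comparison, but they test only within-arm change and, with no untreated arm, show neither efficacy nor comparability

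*Protocol article*

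**What the plan says.** The Data Analysis section calls the study confirmatory and says that "a comparative analysis between both groups’ questionnaire scores will be conducted at all data collection time points using group and paired two-tailed" *t* tests. Group and paired tests thus appear together as one comparison of the two groups. The preceding sentences plan linear and binomial regression over the four time points, controlling for age and gender; treatment arm is not named as a term.

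Under Participants, eligible patients choose their arm: "participants will choose between the e-CBT program (n=55) or the in-person CBT offered individually through this program at Hotel Dieu Hospital (n=55". No matching is described. The comparator is in-person CBT, and there is no untreated or waitlist arm.

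The abstract's Objective reads "It is hypothesized that the e-CBT program will offer results comparable with those of the in-person treatment program". Study Design adds "Quantitative analyses of e-CBT treatment efficacy will be conducted using standardized and clinically validated symptomology questionnaires", and the Discussion says "If proven feasible and efficacious, a web-based psychotherapy clinic can provide significant financial savings to the health care system". On sample size, Data Analysis says "Using the PHQ-9 as the primary outcome, a 30% change is considered clinically significant", and that 55 per arm is "sufficient for detecting significant results with *P*=.05 and a power of 0.95".

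**The concern.** A paired test needs two scores that belong together. Here the only such scores are one participant's results at two time points. The null hypothesis is then zero mean change over time in that arm, which is not a comparison between groups.

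The trial asks two other questions: whether e-CBT is efficacious, and whether its results are comparable with in-person CBT. Participants enter with a current MDD diagnosis, may be taking medication, and are followed to 6 months. Some fall in score is plausible without any specific effect of e-CBT, and no arm in the design separates that fall from treatment.

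Three misreadings are possible:

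- A significant fall in the e-CBT arm is taken as efficacy.
- Significant falls in both arms are taken as comparability.
- Significance in one arm only is taken as a difference between arms.

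**Working it through.** **The plan's own figure.** The 55 per arm can be neither reproduced nor refuted, because no baseline PHQ-9 mean, SD or SD of change is given. Working back at two-sided 0.05 and power 0.95, the multiplier is 1.960 + 1.645 = 3.605.

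- Between-arm test, n = 55: 3.605 × √(2/55) = 0.69 SD.
- Paired test within an arm, n = 55: 3.605 / √55 = 0.49 SD of change.
- With 38 per arm these become 0.83 and 0.58.

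**Inputs.**

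- From Data Analysis: significance level 0.05, two-tailed tests, and "an anticipated dropout rate of up to 30% was factored in".
- n = 55 per arm, or 55 × 0.70 = 38.5, taken as 38, after dropout.
- Assumed: SD of PHQ-9 change of 5 to 6 points, and the mean changes below.

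**Formula.** For mean change m and SD of change s, dz = m/s. The paired *t* statistic has n − 1 degrees of freedom and noncentrality dz × √n. The figures are probabilities of significance in the direction of improvement. Example: m = 3, s = 6, n = 38 gives dz = 0.50, noncentrality 0.50 × √38 = 3.08, and probability 0.85.

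**Step 1. No specific e-CBT effect, only non-specific change.**

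| Non-specific change | dz (SD 6 to SD 5) | n = 55 | n = 38 |
|---|---|---|---|
| 0 points | 0 | nominal 5% test | nominal 5% test |
| 1 point | 0.17 to 0.20 | 23% to 31% | 17% to 22% |
| 2 points | 0.33 to 0.40 | 68% to 83% | 52% to 67% |
| 3 points | 0.50 to 0.60 | 95% to 99% | 85% to 95% |

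Across 1 to 3 points the range is 17% to 99%.

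**Step 2. e-CBT improves 3 points, in-person CBT 6.** The arms are independent, so the chance that both are significant is the product of the two arm probabilities. The 6-point arm has dz of 1.0 to 1.2 and is significant in more than 99% of trials, so the product is close to the 3-point arm's probability.

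- n = 55: 0.954 (SD 6) to 0.992 (SD 5).
- n = 38: 0.851 (SD 6) to 0.950 (SD 5).

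A between-arm *t* test on change (noncentrality d × √(n/2), with d = 3/s) would detect the 3-point difference at n = 38 with probability 0.58 (SD 6) to 0.73 (SD 5).

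**Step 3. Equal change in both arms.** With 4.5 points in each arm, SD 6 and n = 38, both paired tests are significant in 99% of trials. The both-significant pattern is therefore common whether the arms are equal (99%) or e-CBT achieves half (85%), and it barely tells these cases apart.

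**Step 4. Discordant significance under equal change.** With probability p in each arm, exactly one arm is significant with probability 2p(1 − p).

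| dz in both arms | p, n = 55 | 2p(1 − p) | p, n = 38 | 2p(1 − p) |
|---|---|---|---|---|
| 0.3 | 0.589 | 0.48 | 0.437 | 0.49 |
| 0.4 | 0.830 | 0.28 | 0.671 | 0.44 |
| 0.5 | 0.954 | 0.09 | 0.851 | 0.25 |

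**The case against.** The strongest reply is that the article never gives the paired tests this role. The same sentence plans group *t* tests, which do address the difference between arms, and regression is planned as well. The sentence can be read as group tests between arms and paired tests across time points, loosely condensed. The primary outcomes are defined as changes in symptoms, so reporting within-person change is legitimate. Efficacy is already framed largely as relative to in-person CBT in the abstract's Objective and Methods and in Study Design. An active comparator without an untreated arm is an ordinary design choice. Participants must also stay on the same drug and dosage and may not receive other psychotherapy, which weakens the medication explanation.

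Most of this stands. A reader might infer that the paired tests carry the efficacy or comparability conclusion; no passage says so. A reader might also infer that they will almost always be significant. That depends on how much scores change from all causes: with 1 point of change the chance is only 17% to 31%. For a change equal to the article's own 30%, at n = 38, it is 87% to above 99% with assumed baseline means of 12 to 18 and SDs of change of 4 to 7, and 73% at baseline 10 with SD 7.

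What remains is that a study described as confirmatory places a within-arm test under a between-group comparison and does not say which analysis answers which question. Stable medication does not remove natural remission or regression to the mean.

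**Conclusion.** The point holds in limited form. The paired tests are misplaced in the between-group comparison: they test zero mean change within an arm. Without an untreated arm, their significance shows neither that e-CBT is efficacious nor that the arms are comparable. This follows from the design and needs no assumed figure.

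The size does rest on an assumed SD of change of 5 to 6 points and 38 to 55 patients per arm. Both arms would be significant in 85% to 99% of trials with e-CBT at half the in-person change. A paired test would be significant in 17% to 99% with 1 to 3 points of non-specific change. With equal changes of 0.3 to 0.5 SD, only one arm would be significant in 9% to 49%.

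The documents do not support the stronger claim that the planned conclusion rests on these tests. This is an inexpensive correction to the analysis text; it does not show that the comparison as a whole fails.

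**What to change.** In Data Analysis, take the paired *t* tests out of the between-group comparison. Possible wording:

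> Change from baseline within each arm will be described by its mean and 95% CI and will not be used as evidence of efficacy or comparability. The arms will be compared by the between-arm difference in change from baseline, adjusted for baseline score, with its 95% CI.

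The planned regression could supply this estimate if treatment arm and baseline score are named as terms beside age and gender. Baseline adjustment does not remove confounding from patients choosing their arm.

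In Study Design and the Discussion, word efficacy conclusions as relative to in-person CBT.

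The cost is wording only, with no new data or patients. The downside is that within-arm p values can no longer be cited as evidence of efficacy. The fix does not supply a margin for comparability: a two-sided group test that finds no difference would not show comparable results, and neither would a confidence interval without a margin to judge it against. That has to be settled separately.

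### The hypothesis is comparability of e-CBT with in-person CBT, but the only named between-group comparison is a two-tailed difference test with no margin, so the plan as written cannot confirm its hypothesis

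*Protocol article*

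**What the plan says.** The Study Design section states: "We hypothesize that the e-CBT program will offer results comparable with those of the in-person treatment program regarding symptom reduction and quality of life improvement". The Objective in the abstract says the same. The Data Analysis section opens with "This is a confirmatory study with previously established objectives and analyses".

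The same section then fixes three things that bear on this hypothesis:

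- **Between-group comparison.** The comparison of the two groups' "questionnaire scores will be conducted at all data collection time points using group and paired two-tailed" t tests.
- **Sample size.** 55 per arm "would be sufficient for detecting significant results with" P=.05 and power 0.95, with dropout of up to 30% allowed for. The clinical input is "Using the PHQ-9 as the primary outcome, a 30% change is considered clinically significant". The article does not say whether this change is within an arm or between arms, and does not present it as a margin.
- **Regression.** Linear and binomial regression over the four time points, controlling for demographic variables including age and gender. Its stated purpose is to find variables associated with the outcomes. Treatment arm is not named as a term, and no criterion is attached.

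The article contains no non-inferiority or equivalence margin, no confidence-interval criterion and no other rule for concluding that the programs are comparable.

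**The concern.** A claim of comparability needs evidence that any disadvantage of e-CBT is smaller than some tolerable amount. The null hypothesis of the two-tailed t test is no difference. Rejecting it shows that the arms differ; failing to reject it shows only that the data did not separate them. The paired tests address change within an arm and do not compare arms.

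As the article stands, a non-significant group t test is the only apparent basis on which comparability could be claimed. That result becomes more likely as the sample shrinks, scores get noisier or dropout rises, so imprecision would work in favor of the hypothesis. The stakes are practical: the article's conclusions speak of wider access with no loss in quality of care, and it plans workshops to bring the approach into clinical practice.

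**Working it through.** **Inputs from the article.** 55 per arm; two-sided 0.05; power 0.95; dropout up to 30%. Evaluable per arm after dropout: 55 × 0.70 = 38.5, taken as 38.

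**Assumptions, because the article gives no SD or baseline PHQ-9.** SD 5.5 points, range 5 to 6. A true deficit of 2 or 3 points is used for illustration.

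**1. The plan's own figure.** Without an SD, 55 per arm cannot be rebuilt. It can be inverted: d = (1.96 + 1.645) × √(2/n).

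- 55 analysed: 3.605 × √(2/55) = 0.69 SD
- 38.5 analysed: 3.605 × √(2/38.5) = 0.82 SD

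The figure is attainable, since 38/(1 − 0.30) = 54.3, which rounds up to 55. Read as a two-group comparison, it is a size for detecting a between-arm difference of roughly 0.7 to 0.8 SD.

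**2. How often the planned test is non-significant when e-CBT is truly worse.** Two-sample t test; P(non-significant) = 1 − power at d = deficit/SD.

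| Evaluable per arm | True deficit | SD 5 | SD 5.5 | SD 6 |
|---|---|---|---|---|
| 38 | 2 points | 59% | 65% | 70% |
| 38 | 3 points | 27% | 35% | 42% |
| 55 | 2 points | 45% | 53% | 59% |
| 55 | 3 points | 12% | 19% | 26% |

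**3. Precision.** 95% CI half-width = t(0.975) × SD × √(2/n).

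- 38 per arm, SD 5.5: standard error 5.5 × √(2/38) = 1.262; half-width 1.993 × 1.262 = 2.51 points (2.29 to 2.74 for SD 5 to 6)
- 55 per arm, SD 5.5: standard error 1.049; half-width 1.982 × 1.049 = 2.08 points (1.89 to 2.27)

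A non-significant result can therefore leave a deficit of 2 to 3 points, or more, unexcluded.

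**4. What a margin rule could deliver at this size.** Take an illustrative margin of 2.25 points, which is half of 30% of an assumed baseline mean of 15 (0.5 × 0.30 × 15). With truly equal arms, the chance that the upper 95% limit lies below the margin is about Φ(margin/SE − t).

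- 38 per arm: 2.25/1.262 − 1.993 = −0.21, about 42% (36–49% for SD 6 to 5)
- 55 per arm: 2.25/1.049 − 1.982 = 0.16, about 57% (50–65%)

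At 38 per arm and SD 5.5 the half-width (2.51) exceeds this margin (2.25). Non-inferiority could then be claimed only if e-CBT were observed to be better by more than 2.51 − 2.25 = 0.26 points.

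**The case against.** Four points can be made for the plan.

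- **No stated misreading.** A reader might infer that the investigators intend to treat a non-significant test as proof of comparability. The article never says so. What it supports is narrower: it gives no rule for comparability and names no other between-group test, so non-significance is the only apparent basis. This limit stands.
- **The 30% change.** A reader might take it as a change from baseline, and so as irrelevant to a comparison of arms. The article does not say whether it is within or between arms. It is undefined, and it is not offered as a margin. This also stands, and it is why the 2.25-point margin is only an illustration.
- **The regression.** The t tests are introduced as an addition to a regression, and the abstract's Results section names only the regression. If arm were a covariate, the model would give an adjusted difference with a confidence interval. But the article does not say that arm is included, and it attaches no criterion. This narrows the point without removing it.
- **An unseen analysis plan.** A margin could sit there. But the article itself states the hypothesis, the confirmatory status, the test and the sample-size reasoning, and both the test and the sample size are framed as detecting a difference. The mismatch is in what is written.

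**Conclusion.** The point holds. The article sets out a confirmatory comparability hypothesis, yet the between-group test it names and the sample size it justifies both address a difference. Nothing in it defines how comparability would be concluded, so the plan as written cannot confirm its hypothesis.

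That conclusion needs no numerical assumption. The size of the problem does: it rests on an SD of 5 to 6 points, which is not from the article, and on the full 30% loss leaving 38 per arm. On that basis a true 2-point deficit goes undetected more often than not, and a true 3-point deficit about one time in three. With no dropout and SD 5.5 the figures are 53% and 19%.

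**What to change.** 1. Make one comparison primary: the adjusted e-CBT minus in-person difference in PHQ-9 change (week 12 minus baseline), with its two-sided 95% CI. A positive value means e-CBT is worse. State that arm is a term in the model.
2. Label the t tests at other time points and the paired tests descriptive.
3. If a clinically justified between-arm margin can still be fixed before any arm comparison is run, claim non-inferiority only if the upper CI limit lies below it.
4. Otherwise reword the aim as estimating the difference, and state that a non-significant result is not evidence of comparability. This may be the realistic route: the article reports 52 and 48 patients already recruited to an open-label study, with data collection due to end in March 2021 and regression analyses under way.

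**Cost.** Wording, plus one justified margin if that route is open; no new data. The downside is that an inconclusive result is likely. Under the illustrative 2.25-point margin with truly equal arms, the rule succeeds only about 42% of the time at 38 per arm and 57% at 55. A margin also does not deal with confounding: patients choose their arm, so any statement of comparability remains subject to it. The hypothesis also covers quality of life, so the plan should either give that outcome its own criterion or report it as estimation.
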